## **4.4 STUDY METHODOLOGY**

Haemodynamic data FloTrac/Vigileo device will be downloaded directly from the device via a inbuilt USB port 3-hours postoperatively. This data will include:

- Cardiac output
- Cardiac index
- Stroke volume variation
- Mean arterial pressure
- Heart rate
- Systemic vascular resistance

In addition the following data will be collected:

- Demographic characteristics
- Duration of surgery
- Intraoperative blood transfusion requirements
- Intraoperative fluid balances (type, amount)

- Postoperative fluid balances (type, amount)
- Use of inotropes (type, amount, duration)
- Duration of ICU/HDU stay
- Complications
- Daily body weight
- Pain Scores
- Routine biochemistry and haematology
- Drain output
- Hospital discharge
- Readmission with 30 days
- Intraoperative and 30-day mortality

## 5. STUDY POPULATION

### 5.1 RECRUITMENT PROCEDURE

All patients undergoing pancreaticoduodenectomy will be evaluated preoperatively at the anaesthesia pre-admissions clinic at least 1-2 weeks prior to surgery. Patients will be identified for study entry by the investigators or an anaesthetist or research co-ordinator acting on behalf of the principle investigators by surveillance of patients in the pre-admissions clinic. Patients will be identified from their preoperative medical records and surgical notes.

Inform consent will then be obtained.

### 5.2 INCLUSION CRITERIA

- ✓ All patients > 18 years undergoing pancreaticoduodenectomy

### 5.3 EXCLUSION CRITERIA

- ✓ Age less than 18 years
- ✓ Abnormal pre-operative coagulopathy: INR > 1.5, platelet count < 75 x 10^9/l
- ✓ Severe hepatic insufficiency (bilirubin > 30umol/L, ALP > 300iu/L, ALT > 50iu/L, albumin < 25g/dL, INR > 1.5)
- ✓ Severe renal impairment: serum creatinine > 250ummol/l
- ✓ American Society of Anesthesiologists (ASA) physical status IV or V

### 5.4 CONSENT

A thorough assessment of the participant's competence and capacity to make a valid informed decision will be made by one of the study investigators prior to the patient being recruited. All patients will be deemed competent if they:

1. are able to comprehend and retain information relevant to making the decision
2. understand the information and implications of the decision
3. are able to weigh the information in the balance and arrive at a decision

## 6. PARTICIPANT SAFETY AND WITHDRAWAL

### 6.1 RISK MANAGEMENT AND SAFETY

Recruitment for this study will in no way compromise standard of care for any patient undergoing this procedure. Both groups of patients will undergo an ERAS program, which is standard of care in our institutions for all patients undergoing pancreaticoduodenectomy.

Control patients will have fluid management and inotropic use guided by the routine cardiovascular monitoring in place i.e. arterial line, and central venous catheter, which will be at the discretion of the anaesthetist, who will be blinded to Flotrac data. To ensure the most stringent safety of the study, the anaesthetist will be allowed to have the Flotrac haemodynamic data unblinded if needed for clinical decision-making but patients will be removed from analysis if this occurs.

### 6.2 HANDLING OF WITHDRAWALS

Participants may withdraw from the study at any point for the following reasons: participant has chosen to withdraw from the study, protocol violation, or if the control group anaesthetist is unblinded to the Flotrac haemodynamic data. In these circumstances, the participants will be removed from analysis.

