## **Blinding**

Surgical teams, intraoperative and postoperative nursing staff and patients will be blinded to group assignment, but the anaesthetist will be aware of group designation. Both groups of patients will have the FloTrac/Vigileo device™ connected after insertion of the arterial line. The arterial catheters will be connected to the cardiac output device transducer system and haemodynamic data from the FloTrac device will be collected throughout surgery in all patients.

All transducers will be zeroed to atmospheric pressure at the level of the right atrium. Control patients will have fluid management and inotropic use guided by the routine cardiovascular monitoring in place i.e. arterial line, and central venous catheter, which will be at the discretion of the anaesthetist, who will be blinded to FloTrac data. The Control group anaesthetist will be allowed to have the FloTrac haemodynamic data unblinded if needed for clinical decision making but patients will be removed from analysis if this occurs.

In contrast, GDT patients were managed by an SVV guided protocol to maintain SVV < 20%. The fluid management protocol used for the GDT group is shown above in Figure 2. This percentage of SVV is frequently used in our institution as a target for patients undergoing this procedure. For the GDT group, if SVV remains above 20% for at least 2 min, then a 250 mL bolus of balanced crystalloid (Hartmanns solution or Plasmalyte) or colloid fluid (Albumen) will be given. The SVV will be assessed every 20 seconds via the FloTrac/Vigileo proprietary algorithm. Similar to other GDT studies, the preferred colloid will be albumin secondary to the known effects of improved intravascular repletion and intravascular half life and the theoretical benefit of prolonged stroke volume optimization. In both groups, the administration of blood products will be at the discretion of the anaesthetist, as clinically indicated. There will be no standard protocol for fluid maintenance infusion for either group.

The anaesthetist will have no influence over any aspect of postoperative care management. All clinicians and nursing staff in charge of postoperative care will be blinded to the allocation of patients.

The FloTrac system will be connected to the patient prior to surgical incision and discontinued as soon as the surgery is complete.

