### 6.3 REPLACEMENTS

From our experiences with the 3 pilot studies outlined above, withdrawn participants will be not replaced in the study. This will not have any statistical significance of the sample size for the study.

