## 7. STATISTICAL METHODS

### 7.1 SAMPLE SIZE ESTIMATION & JUSTIFICATION

We will recruit 52 patients in total, 26 patients in the GDT group and 26 patients in the standard group.

This is in keeping with realistic power calculations used in other studies evaluating the use of GDT in patients undergoing major abdominal surgery. Canesson's group in the US detect a 3-day mean length of stay difference between the two groups, with a standard deviation of 3 days in each group, a two tailed alpha of 0.05 and power of 0.80, and calculated that a minimum of 17 subjects were required in each group. They assumed that a similar sample size would be needed to detect a similar difference in time to return of GI function. Also, since they expected similar results between arterial pressure waveform analysis technology used for their study and the oesophageal Doppler technology used for other referenced studies, it was felt that this estimation was appropriate.

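### Randomised patients are removed from analysis for post-randomisation events, one of which can occur only in the control arm; this can bias the length-of-stay comparison by an amount and in a direction the protocol does not allow one to know

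*Protocol*

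**What the plan says.** The removal rule appears three times in the protocol.

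- **Section 4.3, Blinding.** Both arms have the device connected, and the control anaesthetist is normally blind to its readings. An exception is allowed: "The Control group anaesthetist will be allowed to have the FloTrac haemodynamic data unblinded if needed for clinical decision making". The same sentence then removes those patients from the analysis.
- **Section 6.1.** The exception is repeated as a safety provision, with the same consequence: "patients will be removed from analysis if this occurs".
- **Section 6.2.** The triggers are "participant has chosen to withdraw from the study, protocol violation, or if the control group anaesthetist is unblinded to the Flotrac haemodynamic data". The consequence is "In these circumstances, the participants will be removed from analysis".

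Section 6.3 adds that "withdrawn participants will be not replaced in the study" and comments: "This will not have any statistical significance of the sample size for the study".

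On numbers, section 7.1 says: "We will recruit 52 patients in total, 26 patients in the GDT group and 26 patients in the standard group". Section 7.2 derives a minimum of 21 per group and adds 5 per group, giving the large SD as the reason. The protocol names no intention-to-treat analysis, second analysis set, sensitivity analysis or expected removal rate, and does not define a protocol violation.

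**The concern.** Randomisation makes the arms comparable at the moment of allocation. Dropping patients for what happens afterwards keeps that protection only if the dropping is unrelated to both arm and outcome. Here one trigger is tied to arm by construction: a GDT patient cannot be removed because the anaesthetist saw the FloTrac data, since those data drive the treatment. The trigger is also tied to clinical need, which may mark patients who will stay longer. The person whose decision leads to removal knows the allocation (section 4.3).

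The primary comparison could then be between all GDT patients and a control arm with some of its harder cases taken out. Removal for protocol violation could distort either arm. The protocol itself fixes this rule, so a statistical analysis plan that kept everyone in would contradict it.

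**Working it through.** **1. The plan's own sample size.** Inputs from section 7.2 and its table: difference 2.5 days, SD 4 in group 1 and 0.0 in group 2, two-sided 5%, power 80%.

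n = (4² + 0²) × (1.960 + 0.842)² / 2.5² = 16 × 7.849 / 6.25 = 20.09, rounded up to 21 per group.

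The printed 21 is reproduced, but only with the group 2 SD at 0.0. That is a separate problem. Below, SD 4 is used in both arms.

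**2. Effect of fewer patients, with no bias.** Two-sample t-test, SD 4 in both arms, two-sided 5%:

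| Analysed (GDT v control) | Power, 2 days (text) | Power, 2.5 days (table) |
|---|---|---|
| 26 v 26 | 42% | 60% |
| 26 v 21 (5 controls removed) | 39% | 55% |
| 21 v 21 | 35% | 51% |

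Removals do cost power, but only a few points.

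**3. Bias from control-only removal.** Suppose a share f of controls is removed and would have stayed D days longer than the controls who remain. The full control mean equals the remaining mean plus f × D, so removal lowers the control mean by f × D. The protocol gives neither f nor D; both are assumptions.

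| Removed | f | D = 5 | D = 10 |
|---|---|---|---|
| 2 of 26 | 7.7% | 0.38 days | 0.77 days |
| 3 of 26 | 11.5% | 0.58 days | 1.15 days |
| 5 of 26 | 19.2% | 0.96 days | 1.92 days |

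**4. How large D can be.** A split of this kind contributes f(1 − f)D² to the variance, and the total is 4² = 16. With f = 5/26, D cannot exceed 4 / √(0.192 × 0.808) = 10.1 days, which caps the bias at 0.192 × 10.1 = 1.95 days. So D = 10 is about the largest value consistent with the plan's SD when five are removed.

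**5. Effect on power, one example.** Take f = 3/26, D = 10 and a true effect of 2 days.

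- Effect left: 2 − 1.15 = 0.85 days.
- Variance used by the split: 0.115 × 0.885 × 100 = 10.2. The remaining controls have variance 16 − 10.2 = 5.8, SD about 2.4.
- Standard error: √(5.8/23 + 16/26) = 0.93.
- Power, normal approximation: Φ(0.91 − 1.96) + Φ(−0.91 − 1.96) = about 15%.

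Without removal, power is 42% by the t-test, or 44% by the same normal approximation.

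**6. False positives.** A simulation with no true effect was run: 10,000 trials, 26 per arm, within-group SD 4, and controls removed with probability p when their stay was D days longer. The two-sided error was 6.3% (p = 10%, D = 4), 8.7% (10%, 8), 9.6% (20%, 4) and 19.2% (20%, 8), against a nominal 5%. In this set-up total variance exceeds 16, so it is not the same scenario as steps 4 and 5.

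**7. Section 6.3 against the rest.** The five extra patients per group are attributed in 7.2 to the SD, not to attrition. Section 6.3 appeals to the three pilot studies, which section 2.3 describes as retrospective and observational. Such studies cannot show how often patients in a randomised trial withdraw or are unblinded.

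**The case against.** The best defence is that everything about size is assumed. The documents give no unblinding rate, violation rate or excess stay, and say only that the data may be revealed when clinically needed. Unblinding may be rare, and the unblinded patients need not be the ones who stay longest. The 26 per group also leaves room for five removals before the stated minimum of 21 is reached. All of this stands. It makes the bias potential, and it makes the shrinkage a minor point.

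Several stronger readings are tempting but not supported:

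- **That the bias could exceed the target effect.** Five removals with a 15-day excess would give 5/26 × 15 = 2.9 days. But that split alone adds a variance of 0.192 × 0.808 × 225 = 34.9, more than twice the planned 16. The 7 to 140 day range in the pilot series (section 2.3) makes a larger real SD plausible, but a larger bias would have to be argued on that larger SD.
- **That the bias certainly runs against GDT, or that violations certainly offset it.** The first requires unblinded controls to be the harder cases. The second reads an undefined term as meaning GDT patients who could not be managed to protocol; it could equally cover controls or late eligibility errors.
- **That the damage cannot be repaired in analysis.** Section 4.4 collects hospital discharge, so an all-randomised analysis is feasible. Only the restricted comparison is beyond repair.
- **That removals would reveal allocation to the blinded statistician.** Section 7.3 does not say what removal information the statistician receives.

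**Conclusion.** The rule is wrong as written and should be changed before analysis. Its arm-specific, need-driven trigger can bias the primary comparison, and nothing in the protocol provides an unrestricted analysis to set beside it.

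On the stated assumptions (2 to 5 of 26 controls removed, excess stay 5 to 10 days, SD 4), the control mean would fall by about 0.4 to 1.9 days, against a target of 2 days in the text or 2.5 in the table. This would mask a GDT benefit if unblinded controls are the longer stayers. Once violations and withdrawals are included, the net direction is unknown.

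The bias matters more than the lost numbers. The sample-size remark in 6.3 is unsupported, but power lost through shrinkage alone is small beside the shortfall already present at 26 per arm with SD 4 in both arms.

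**What to change.** Replace the removal sentences in sections 4.3, 6.1 and 6.2 with wording to this effect:

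*All randomised patients are analysed in the arm to which they were assigned. Control patients whose FloTrac data are revealed, and patients with protocol violations, remain in the analysis; these events are recorded and reported by arm. For patients who withdraw, length of stay is taken from the hospital record unless consent to use it is withdrawn.*

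Keep the current exclusion set only as a per-protocol sensitivity analysis, and delete the last sentence of section 6.3.

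The cost is protocol wording: the outcome is in the hospital record and the anaesthetist's access to the data is untouched. The one drawback is that unblinded controls kept in the analysis may slightly dilute the contrast between arms. The sensitivity analysis would show by how much the result depends on them.

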### 6.3 REPLACEMENTS

From our experiences with the 3 pilot studies outlined above, withdrawn participants will be not replaced in the study. This will not have any statistical significance of the sample size for the study.

## 7. STATISTICAL METHODS

### 7.1 SAMPLE SIZE ESTIMATION & JUSTIFICATION

We will recruit 52 patients in total, 26 patients in the GDT group and 26 patients in the standard group.

This is in keeping with realistic power calculations used in other studies evaluating the use of GDT in patients undergoing major abdominal surgery. Canesson's group in the US detect a 3-day mean length of stay difference between the two groups, with a standard deviation of 3 days in each group, a two tailed alpha of 0.05 and power of 0.80, and calculated that a minimum of 17 subjects were required in each group. They assumed that a similar sample size would be needed to detect a similar difference in time to return of GI function. Also, since they expected similar results between arterial pressure waveform analysis technology used for their study and the oesophageal Doppler technology used for other referenced studies, it was felt that this estimation was appropriate.

### 7.2 POWER CALCULATIONS

Sample size for the study was calculated based on our pilot data evaluating patients undergoing pancreaticoduodenectomy with an ERAS program at Austin hospital. With a median length of hospital stay of 16 days, and a SD of 4 days, if we were to demonstrate a mean difference between the control group and the GDT group of 2 days, with a power value

of 80%, we require a minimum of 21 patients to be recruited into each group. We will recruit 5 additional patients in each group, given the large SD.

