**Table 1: Summary of major and minor complication rates in patients undergoing colorectal and non-colorectal major abdominal procedures**

|                                         | All operations | Colorectal | Non-colorectal | p |
|-----------------------------------------|----------------|------------|----------------|----------|
| Patients with at least one complication | 57 (57%)       | 28 (43%)   | 29 (82%)       | 0.003    |
| Patients with major complications       | 32 (32%)       | 14 (21%)   | 18 (51.4%)     | 0.004    |
| Patients with minor complications       | 52 (52%)       | 27 (41.5%) | 25 (71.4%)     | 0.009    |
| Number of overall minor complications   | 104            | 46         | 58             | 0.003    |
| Number of overall major complications   | 63             | 23         | 40             | 0.012    |
| Major cardiac complications*            | 10             | 4          | 6              | 0.78     |
| Respiratory complications §             | 30             | 11         | 19             | 0.001    |
| Tissue healing complications ¶          | 20             | 8          | 12             | 0.012    |
| Total hospital days - mean (SD)         | 18 (30)        | 12         | 30             | 0.004    |

\* pulmonary oedema causing sudden death or CT/scintigraphic changes, myocardial infarction (ECG changes and myocardial enzyme elevation: cTropI>.06), ventricular arrhythmia (ECG changes/medical treatment or cardioversion), heart rate <50b/min requiring medical treatment/pacing)§ pulmonary embolism (causing sudden death or CT/scintigraphic changes), pneumonia (elevated temperature with radiographic changes), pulmonary congestion (shortness of breath, crepitations & medical treatment), pneumothorax (requiring drainage)

¶ anastomotic leakage, necrosis of stoma, superficial wound infection (surgical evacuation of pus or haematoma/secondary suture)

The authors then evaluated whether an Enhanced Recovery After Surgery program (ERAS) reduced length of hospital stay following uncomplicated pancreaticoduodenectomy. We hypothesized that patients undergoing uncomplicated pancreaticoduodenectomy treated by an Enhanced Recovery After Surgery (ERAS) program would have a shorter length of hospital stay compared to those managed by standard care. Patients without surgical or medical complications following pancreaticoduodenectomy managed by ERAS or standard

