**Study Name:** A Prospective Multicentre Randomized Controlled Trial of Standard Compared to Goal-directed Therapy (GDT) for Patients Undergoing Pancreaticoduodenectomy

9

programs between 2005 and 2011 were identified and prognostic predictors for length of hospital stay determined. Forty-one patients treated by pancreaticoduodenectomy had no medical or surgical complications during this period. Of these patients, 20 underwent ERAS program compared to 21 who underwent standard care. Median postoperative length of stay was shorter in the ERAS group (8 days, range: 7-16 days) *versus* 14 days, range: 8-29 days;  $P<0.001$ ). There were three readmissions in the ERAS program related to abdominal pain and none in the standard group. The overall length of stay, accounting for readmissions, still remained significantly shorter in the fast track recovery program group (median 9 days, range: 7-17 days *versus* median 14 days, range: 8-29 days;  $P<0.001$ ). Patients in the standard group were more likely to have a feeding jejunostomy tube ( $P<0.001$ ), pylorus preserving procedure ( $P=0.001$ ) and a nasogastric tube in place longer than 24 hours postoperatively ( $P<0.001$ ). There were no significant differences in discharge destination between groups. On multivariate analysis, the only factor independently associated with postoperative discharge by day 8 was ERAS program (OR: 37.1, 95% CI: 4.08-338;  $P<0.001$ ). We concluded that ERAS program achieved significantly shorter length of stay following uncomplicated pancreaticoduodenectomy.

**Table 2. Austin Hospital Data: Factors associated with discharge following pancreaticoduodenectomy by post-operative day 8**

|                                       | 8 Days or less LOS (n=14) | More than 8 days LOS (n=27) | Univariate                       |                      | Multivariate                     |                      |
|---------------------------------------|---------------------------|-----------------------------|----------------------------------|----------------------|----------------------------------|----------------------|
|                                       |                           |                             | Odds ratio (Confidence interval) | Difference (p value) | Odds ratio (Confidence interval) | Difference (p value) |

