| Negative fluid balance
day 3 post surgery               | 20(50%)           | 11(55%)                    | 9(42%)                   | 0.437                   |
| Readmissions                                               | 3(7%)             | 3(15%)                     | 0(0%)                    | 0.107                   |
| Initial post-operative
length of stay (days)            | 10(7-29)          | 8(7-16)                    | 14(8-29)                 | <0.001*                 |
| Overall length of stay
including readmissions
(days) | 10(7-29)          | 9(7-16)                    | 14(8-29)                 | <0.001*                 |

SICU – Surgical intensive care unit; Missing values – nasogastric tube removal day 1 post surgery =1;  
\*p≤0.05 Chi-Square/Fisher's exact test

Finally we evaluated whether liberal fluid intervention and positive fluid balance affect length of hospital stay following pancreaticoduodenectomy (Whipple's Procedure). The rationale for this study is that the effects on detailed fluid intervention on perioperative complications and length of hospital stay (LOS) after pancreaticoduodenectomy have not been reported. We hypothesized that patients undergoing pancreaticoduodenectomy treated with a liberal fluid regime would have a longer LOS compared to those managed with a restrictive regime. We conducted a retrospective analysis of patients undergoing pancreaticoduodenectomy at Austin Hospital. Demographic data, operative details, detailed fluid prescription, complications and outcomes were retrieved from medical records. Prognostic predictors for LOS were determined. Data for 150 consecutive patients undergoing pancreaticoduodenectomy between 2004 - 2012 was collected. Mean age: 66 years; Male gender: 59%, Mean weight: 74kg, ASA Class 3: 75%. Average volume of intravenous fluid administered on postoperative days (POD) 1 to 3 was 3.0L (range: 0.9-14.1), 2.1L (range: 0.3-6.1), and 1.7L (range: 0-6.0) respectively. 50 patients (33%) experienced at least one major complication; 66 patients (44%) at least one minor complication. Common complications: sepsis (22%), anastomotic leak (20%), pneumonia (17%), delayed gastric emptying (17%), myocardial infarction (8%), pulmonary oedema (6%). 30-day mortality: 2%. Median LOS: 17 days (range: 7-140 days).

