### **Summary of power calculations for this study**

|                                        |                |     |                |                                    |
|----------------------------------------|----------------|-----|----------------|------------------------------------|
| Confidence Interval (2-sided)          |                | 95% |                |                                    |
| Power                                  |                | 80% |                |                                    |
| Ratio of sample size (Group 2/Group 1) |                | 1   |                |                                    |
|                                        | Group 1 |     | Group 2 | Mean difference |
| Mean                                   | 16             |     |                | 2.5                                |
| Standard deviation                     | 4              |     | 0.0            |                                    |
| Variance                               | 0.0            |     | 0.0            |                                    |

|                        |    |  |
|------------------------|----|--|
| Sample size of Group 1 | 21 |  |
| Sample size of Group 2 | 21 |  |
| Total sample size      | 42 |  |

 Mean difference= (Group 1 mean) - (Group 2 mean)

*RESULTS FROM OPENEPI, VERSION 2, OPEN SOURCE CALCULATOR--SSMEAN*

<http://www.openepi.com/OE2.3/SampleSize/SSMean.htm>

Source file last modified on 09/21/2010 13:10:35

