## **7.3 STATISTICAL METHODS TO BE UNDERTAKEN**

Statistical analysis will be performed using computerized software (SPSS for Windows version 12.0). For data that was non-normally distributed a Mann–Whitney test was used and normally distributed data were compared using the Student T test. Ordinal and nominal data were compared using Chi square analysis. A p-value <0.05 will be considered significant. Standard statistical tests will be used, and an independent statistician blinded to the randomisation will undertake all statistical analyses.

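### The planning values in section 7.2 (centre 16 days, SD 4) are not supported together by any pilot group the protocol reports, so the 80% power claim is unsupported

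*Protocol*

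**What the plan says.** Section 7.2 attributes its inputs to the institution's pilot data on pancreaticoduodenectomy with ERAS: "With a median length of hospital stay of 16 days, and a SD of 4 days". The target is a "mean difference between the control group and the GDT group of 2 days", and the result is given as "of 80%, we require a minimum of 21 patients to be recruited into each group". Five more per group are added because the SD is considered large, which gives 26 per arm (section 7.1). The calculator summary that follows enters 16 as a mean and shows a difference of 2.5 days.

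Section 2.3 reports length of stay for three pilot studies:

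- First study, 100 major gastrointestinal operations (Table 1): "Total hospital days - mean (SD) | 18 (30").
- Second study, 41 pancreaticoduodenectomies, all without complications: "Median postoperative length of stay was shorter in the ERAS group (8 days, range: 7-16 days"), against a median of 14 (8-29) under standard care.
- Third study, 150 consecutive pancreaticoduodenectomies, 2004-2012: "Median LOS: 17 days (range: 7-140 days").

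Section 5.2 admits adults undergoing pancreaticoduodenectomy, subject to the exclusions in 5.3. It does not select for an uncomplicated course. Section 7.3 plans a t-test for normal data and a Mann-Whitney test otherwise.

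**The concern.** Length of stay is the primary outcome, and section 7.2 is the only calculation for this trial. Its two inputs appear to describe different patients. A centre of 16 resembles the all-comer cohort, while an SD of 4 resembles patients who had no complications. In the all-comer cohort 33% had a major complication, and section 2.3 reports complications as independently associated with length of stay. Having fewer complications is also part of the trial hypothesis. The long upper tail therefore belongs to what the trial will observe.

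If the spread is understated, the real power is well under the advertised 80%, and a null result would say little about the device. Correcting only the calculator entries would not cure this, because the corrected sample size would still rest on an SD that cannot be traced.

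**Working it through.** **Inputs.** Two-sided alpha 0.05 ("A p-value <0.05 will be considered significant"; "Confidence Interval (2-sided")), power 80%, 1:1 allocation, differences of 2 days (text) and 2.5 days (calculator summary), 26 per arm.

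**1. The plan's own figure.** n per arm = (SD1² + SD2²)(1.960 + 0.842)² / d², where the squared sum is 7.849.

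- SD 4 in both arms, d = 2: 32 × 7.849 / 4 = 62.8, so 63 per arm.
- SD 4 in both arms, d = 2.5: 32 × 7.849 / 6.25 = 40.2, so 41 per arm.
- As printed in the summary (SD 4 and 0.0, d = 2.5): 16 × 7.849 / 6.25 = 20.1, so 21 per arm.

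The stated 21 arises only with a zero SD in group 2. That is a separate error. It means that 80% is not reached even if SD 4 is accepted.

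**2. Can any reported group be the source of 16 and 4?**

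- *ERAS, uncomplicated (n = 20, median 8, range 7-16).* An SD from 1.8 to 4.5 is possible, so 4 fits. The centre does not. The largest possible mean has one value at 7, ten at 8 and nine at 16: (7 + 80 + 144) / 20 = 11.55. Sixteen is this group's maximum.
- *Standard care, uncomplicated (n = 21, median 14, range 8-29).* An SD from 3.6 to 10.5 is possible, but the group is not ERAS and its median is 14.
- *All 41 uncomplicated (median 10, range 7-29).* An SD from 3.0 to 11.1 is possible, but the median is 10.
- *All-comers (n = 150, median 17, range 7-140).* The centre is close to 16. The smallest SD that fits has one value at 7, 75 at 17, 73 at 18.5 and one at 140. The mean is 2772.5 / 150 = 18.48, the sum of squares is 15,063, and SD = √(15,063 / 149) = 10.05. SD 4 is impossible here.
- *Mixed gastrointestinal surgery (n = 100).* Mean 18, SD 30. From the Table 1 percentages, about 65 were colorectal (27 / 0.415), so this says little about pancreaticoduodenectomy.

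**3. Power with 26 per arm.** t-test with 50 degrees of freedom and noncentrality d / (SD × √(2/26)). The difference detectable at 80% power is 0.792 × SD.

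| SD | Power, 2 days | Power, 2.5 days | Detectable difference |
|---|---|---|---|
| 4 | 42% | 60% | 3.2 days |
| 7 | 17% | 24% | 5.5 days |
| 10 | 11% | 14% | 7.9 days |
| 15 | 8% | 9% | 11.9 days |

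By the formula in step 1, 80% power at SD 10 would need 393 per arm (2 days) or 252 (2.5 days).

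**4. Mann-Whitney test, simulated, 26 per arm, pure shift.**

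- Assumed 6 days plus a lognormal, median 17, log-SD 0.6 to 0.9 (SD about 9 to 18): about 12-22% for 2 days and 18-28% for 2.5 days.
- Assumed normal (17, SD 4) for 149 of 150 patients and 140 days for the remaining one (overall SD 10.8): about 39% for 2 days and 55% for 2.5 days.

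**The case against.** The strongest reply is that the floor of 10 is nearly all one patient. In the minimising arrangement the 140-day stay supplies 14,766 of the 15,063 sum of squares. One value at 7 and 148 at 17 have an SD of only 0.82. At a frequency of 1 in 150, a sample of 52 contains no such stay with probability (149/150)^52, about 71%. The cohort also spans 2004-2012, and the second study shows standard-care patients in 2005-2011 staying longer, whereas both trial arms follow ERAS and the section 5.3 exclusions apply. An all-comer ERAS subset with a smaller SD may exist without being tabulated. All of this stands.

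It limits what may be inferred. A reader might conclude any of the following, and the documents do not support them:

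- *SD 4 contradicts every length-of-stay figure in the protocol.* It is possible within the 41 uncomplicated patients and close to the SD of 3 used by the outside trial cited in section 7.1. Likewise, 16 is one day from 17.
- *The trial population's SD must be at least 2.5 times the planned one.* A minimum for one historical cohort is not a minimum for ERAS patients who meet the trial criteria.
- *A difference of 2 to 2.5 days cannot be detected.* The 11% and 14% assume normal data and a t-test, while section 7.3 allows Mann-Whitney, which reaches about 39% and 55% in the outlier case.
- *The SD of 30 describes pancreatic surgery.* It comes from the first study, in mixed gastrointestinal surgery.

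None of this restores 80%. The most favourable scenario examined, SD 4 with a 2.5-day difference, gives 60%.

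**Conclusion.** The concern holds in this form: the pair 16 and 4 cannot be traced to any reported group. Among the protocol's own pilot groups, an SD near 4 fits only patients selected for having no complications, while the trial enrols all eligible patients. A median also stands in for a mean in a skewed outcome. The 80% claim is therefore unsupported.

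Power with 26 per arm is 42% (2 days) or 60% (2.5 days) at the protocol's own SD, and falls to about 8-9% at SD 15. Mann-Whitney scenarios give about 12% to 55%. The SDs of 7, 10 and 15 and the simulated distributions are assumptions that bracket what is unknown, not estimates for this trial. All figures take 26 analysed per arm. Sections 6.2 and 6.3 remove withdrawn patients without replacing them, so the analysed number may be lower.

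**What to change.** Derive the centre and spread, on the raw and log scales, from pilot patients who match the trial: all-comers, ERAS, meeting the eligibility criteria. Cite that dataset in section 7.2, report mean and median separately, and restate power and detectable difference for 26 per arm on the scale of the planned test. Use one target difference in the text and in the calculator summary.

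If no matching subset exists, show power for a range of SDs, for example 4, 7, 10 and 15, and drop the 80% claim.

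The cost is a few hours of analysis, if the sponsor can pull these patients from its pilot data, and revised wording. The downside is a less favourable stated power.
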